**Fig. 1 Fig1:**
[figure not shown]
SPIRIT diagram showing participant involvement. *CRP* C-reactive protein

#### Unblinding

There are three scenarios that may lead to unblinding of treatment assignment:Clinical deterioration in the patient on day 6 or later after randomization, possibly consistent with worsening CAP, orThe occurrence of a clinically significant adverse event plausibly related to amoxicillin administration on day 6 or later after randomizationCaregiver-initiated withdrawal of the participant from the study at day 6 or later up until the clinical evaluation at day 14–21, if requested by the caregiver

When the RA is made aware of participant difficulties consistent with scenario 1 or 2, the RA will inform the local PI or delegate, who may recommend participant re-evaluation, either in the ED or in a hospital clinic where another study physician can evaluate the participant properly. If unblinding is required, this information can be provided to the physician evaluating the study participant following authorization by the local PI or their delegate.

### Laboratory testing

#### Microbiology testing

All nasopharyngeal specimens acquired at baseline will be tested for the following:Eleven different respiratory viral pathogens (influenza A, influenza B, RSV A/B, parainfluenza virus I-III, rhinovirus, enterovirus, adenovirus, and human metapneumovirus) using the laboratory-developed multiplex PCR platform in clinical use at McMasterThree different atypical respiratory pathogens (*Legionella pneumophila, M. pneumoniae,* and *Chlamydophila pneumoniae*) using a multiplex loop-mediated isothermal amplification (LAMP) platform*S. pneumoniae* incidence density (uniplex laboratory-developed PCR using a *lytA* target)

Enteric samples will be requested to establish baseline intestinal microbiome composition and to assess colonization with antibiotic resistant organisms (AROs), namely ampicillin-resistant *Escherichia coli* and *Enterobacteriaceae* with extended-spectrum beta-lactamase (ESBL) production. These samples will either be bulk stool or rectal swabs collected using flocked rectal swabs (Copan Italia S.A.) and eluted using Cary Blair and/or eNAT transport medium. Enteric samples can be collected up to 24 h post-visit, as necessary. Another enteric sample will be collected during or immediately subsequent to the primary outcome visit. Finally, caregivers will be asked to collect a final set of enteric samples for intestinal microbiome analysis and/or ARO colonization measurement 3–6 months post-enrolment. All laboratory specimens will be stored at -80 °C until testing occurs. Enteric specimens will have 16S ribosomal RNA (rRNA) profiling conducted, with baseline samples compared to samples collected at the primary outcome visit and then later at 3–6 months post-enrolment.

#### Other testing

If blood work was ordered by the attending ED physician, results of complete blood count and/or CRP will be noted but no additional blood draws will be taken as part of study activities. For those participants who did not have serum CRP measured, an optional salivary sample will be requested for salivary CRP measurement; this will be acquired using a small sponge (Salimetrics Children’s Sponge) placed in the buccal mucosa or beneath the tongue (for 60–90 seconds).

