#### Tertiary

The tertiary objectives are to evaluate the following epidemiological features in children diagnosed with mild CAP in the current era of universal vaccination with the 13-valent pneumococcal vaccine (PCV13) and include:To investigate various baseline characteristics in a cohort of children meeting study criteria for CAP, including the distribution of saliva C-reactive protein (CRP) values, the prevalence of *Streptococcus pneumoniae* high-level colonization (>10 000 genome copies/mL), in nasopharyngeal swab (NPS) specimens, how frequently *Mycoplasma pneumoniae* is detected in NPS samples, and what proportion of study participants with alveolar consolidation documented on chest radiograph have NPS specimens positive for at least one virus.To investigate whether these baseline characteristics differ substantially when stratified by age group (6–59 months vs. 5–10 years of age).To explore whether any of these baseline characteristics appear to be more common in children who do not achieve early clinical cure.

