### Study procedures

#### Screening, enrolment, and randomization

Attempted recruitment will be triggered in the ED as soon as a child of the appropriate age is diagnosed with CAP by the ED physician during study hours. All participants will be provided with the appropriate medications and nasopharyngeal, salivary, and enteric specimens will be collected; note that participants can opt out of providing any of these specimens and still participate in the trial. The interpretation of the chest radiograph by the radiologist will be abstracted and recorded.

All eligible participants will be assigned a study ID. Randomization of the participants will be completed using a randomization scheme (stratified by site) generated by the study pharmacy at MCH using a random number generator, using block sizes of 2 and 4, and will pre-assign kit contents to a given study ID. The RA will notify the site study pharmacy after a successful recruitment and will communicate the study ID so that the appropriate medications can be prepared by the research pharmacist; for the duration of the study, the pharmacist will be the only individual not blinded to the participant’s treatment allocation. All participants will be given an initial 5 days of amoxicillin to begin. For potential participants at MCH who present at a time when an RA is not available, the attending ED physician will prescribe amoxicillin at the study dose (i.e. the standard of care) and obtain consent for subsequent RA contact and potential enrolment within 24 h after ED discharge. Recruitment at CHEO will only proceed between 10.00 a.m. and 10.00 p.m. daily. Participants will be given all study medications at enrolment unless a participant presents outside of pharmacy operational hours at MCH; in that instance, the RA will dispense an after-hours open-label amoxicillin kit for the first 5 days of treatment to the caregiver and contact the pharmacy with the study ID so that the blinded medication kit can be prepared and provided to the caregiver at a later date (prior to day 6).

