These analyses will be exploratory. The following sensitivity analyses are planned: (1) intention-to-treat analysis; (2) strict per-protocol analysis including only those participants who were adherent to their medications and whose radiographs were reported by a radiologist to demonstrate alveolar infiltrates; (3) per-protocol analysis stratified by whether the saliva CRP was greater than the 75th percentile; and (4) per-protocol analysis stratified by whether a virus, an atypical pathogen, or high-level *S. pneumoniae* colonization was found in the NPS. If evidence is found of effect modification or confounding related to the above parameters additional analyses will be undertaken. The results of all analyses will be reported as estimate of effect, corresponding 95% CI and associated *p* values. All *p* values will be reported to three decimal places with those less than 0.001 reported as *p* < 0.001. The criterion for statistical significance will be set at alpha = 0.05. Table 1 provides a summary of the outcomes, corresponding hypotheses, measure, and method of analysis.

**Table 1 Tab1:** Variables, measures, and methods of analysis

Variable/outcome	Hypothesis	Outcome measure	Methods of analysis
Primary			
Clinical cure (per-protocol)	Short-course (5-day) treatment with high-dose amoxicillin is non-inferior to long-course (10-day) treatment	At visit (day 14–21) composite of: 1. Defervesced on or before day 4 2. No more than 1 further fever spike until visit 3. No tachypnoea and decreased work of breathing 4. No additional antibacterials given Dichotomous	Logistic regression
Secondary, between-group comparisons			
Absenteeism (caregiver, from work)	Short-course treatment is non-inferior to long-course treatment	Daily symptom diaries: self-reported number of caregiver-days absent from work (count)	Poisson regression
Absenteeism (child, from daycare/school)	Short-course treatment is non-inferior to long-course treatment	Daily symptom diaries: reported number of child-days absent from daycare/school (count)	Poisson regression
Mild drug adverse reactions	Fewer in short-course arm than in long-course arm	Daily symptom diaries: Reported number of child-days with diarrhoea, rash, abdominal pain, yeast infection (count)	Poisson regression
Anaphylaxis and other severe drug adverse reactions	Fewer in short-course arm than in long-course arm^a^	Daily symptom diaries, SAE reports. Dichotomous	Descriptive statistics

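### Two sections disagree on who is asked for saliva; under the narrower rule, children with a serum CRP have no value in the salivary-CRP analyses

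*Protocol article*

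**What the plan says.** In the Protocol article, Screening, enrolment, and randomization: "All participants will be provided with the appropriate medications and nasopharyngeal, salivary, and enteric specimens will be collected". The one exception given there is that "participants can opt out of providing any of these specimens and still participate in the trial". A serum result is not mentioned.

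Under Laboratory testing, Other testing, serum CRP is whatever routine care produced: "If blood work was ordered by the attending ED physician, results of complete blood count and/or CRP will be noted", with no blood drawn for the study. The next sentence sets the saliva rule: "For those participants who did not have serum CRP measured, an optional salivary sample will be requested".

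The analyses that use the measurement all name saliva:

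- Tertiary objective: baseline characteristics "in a cohort of children meeting study criteria for CAP, including the distribution of saliva C-reactive protein (CRP) values". Table 1 lists this distribution under its entire-cohort heading, as a mean with 95% CI.
- Secondary outcomes: whether cure rates depend on baseline salivary CRP.
- Subgroup objective, Analysis section and Table 1: a treatment interaction for higher against lower salivary CRP.
- Sensitivity analysis 3: "per-protocol analysis stratified by whether the saliva CRP was greater than the 75th percentile".

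**The concern.** The two collection rules cannot both be followed for a child who already has a serum CRP. One has the research assistant ask for saliva; the other does not.

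If staff follow the laboratory section, the missing group is created by the design and not by refusal. It is also selected by a clinician, because a serum CRP exists only where the ED physician chose to order it. The Discussion says that blood work is seldom requested in many regions unless pneumonia is severe, which links testing to perceived severity. If tested children do have higher CRP, the cohort mean and the 75th-percentile cut-point are too low, and the high-CRP stratum is thinned. Table 1 expects lower cure in that stratum, and its hypothesis for the cohort mean (above bronchiolitis, below empyema) would be tested on a selected group.

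**Working it through.** **1. The two rules side by side**

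| Child at enrolment | Enrolment section | Other testing |
|---|---|---|
| No blood work | saliva, may opt out | saliva, optional |
| Blood count only | saliva, may opt out | saliva, optional |
| Serum CRP measured | saliva, may opt out | not requested |

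The rules differ only in the last row. Having blood work does not itself remove a child; having a serum CRP does.

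**2. Does serum CRP enter any analysis?** The tertiary, secondary, subgroup and sensitivity analyses and Table 1 all specify saliva. The research question in the Background speaks of the CRP level without naming a source, but nothing later uses this to bring serum values in or to put the two measurements on one scale.

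**3. The denominator.** The only related figure is the sample size: 5% failure in both arms, margin 7.5%, one-sided alpha 0.025, power 0.80.

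n per arm = (1.960 + 0.842)² × 2 × 0.05 × 0.95 / 0.075² = 7.849 × 0.095 / 0.005625 = 132.6, so 133 per arm (266 in total).

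The article states 135 per arm (270 in total), which agrees to within 2 per arm. The point does not depend on this; 270 is used below as the cohort size.

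**4. Size of the loss, under assumptions.** The documents give neither the share q with a serum CRP nor the difference in CRP between tested and untested children. I take log CRP as normal with SD 1 within each group, and let tested children average s SD higher.

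- The full-cohort 75th percentile c solves q[1 − Φ(c − s)] + (1 − q)[1 − Φ(c)] = 0.25.
- Share of the full-cohort top quartile without saliva = q[1 − Φ(c − s)] / 0.25.
- The mean among children with saliva is too low by q × s. Their 75th percentile is 0.674, too low by c − 0.674 (both in SD of log CRP).

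Example, q = 0.10 and s = 1: c = 0.795 and 1 − Φ(−0.205) = 0.581, so the share lost is 0.10 × 0.581 / 0.25 = 23%.

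The top quartile of 270 is 270 × 0.25 = 67.5 children. Ranges run from s = 0.5 to s = 1.

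| q | Without saliva (270 × q) | Top quartile lost, s = 0 | Top quartile lost, s = 0.5 to 1 | Children lost from top quartile | Mean too low by (SD) | 75th percentile too low by (SD) |
|---|---|---|---|---|---|---|
| 5% | 13.5 | 5% | 8–12% | 6–8 | 0.03–0.05 | 0.03–0.06 |
| 10% | 27 | 10% | 16–23% | 11–16 | 0.05–0.10 | 0.06–0.12 |
| 20% | 54 | 20% | 31–43% | 21–29 | 0.10–0.20 | 0.11–0.24 |

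All rows are before opt-outs. A simulation of the same model gave the same shares. With s = 0 the loss is proportional, and the mean and percentile are unbiased.

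**5. What is not affected.** A serum CRP ordered in the ED does not depend on the randomised arm. Missing saliva from this cause therefore does not unbalance the arms. It limits which children the CRP results describe.

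**The case against.** The strongest reply is that the enrolment sentence is a general summary and the laboratory section is the operational detail, so there is one rule, stated twice at different depths. Recording serum where it exists and asking for saliva where it does not also reads like a plan to obtain one CRP value per child, and how the two are combined may be set out in the full protocol or SAP. That is a fair reading, and its absence from a journal article is no finding in itself. But it does not explain why every analysis listed in the article names saliva, and no later document can recover a baseline saliva sample that was never requested.

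The second reply is scale, and most of it stands. The trial enrols children well enough for outpatient care, and the Discussion suggests blood work is uncommon in milder disease, so the affected share may be small. The analyses are secondary, tertiary or exploratory. At about 5% failure, 270 children yield 270 × 0.05 = 13.5 failures, so CRP effect modification would be hard to estimate even with saliva from everyone.

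Several stronger readings are tempting but unsupported:

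- That everyone with blood work is lost. A blood count alone does not trigger the exclusion.
- That the saliva percentile is certainly too low. This needs higher CRP in tested children, which is plausible but not stated.
- That the stratum where short treatment in particular fails is removed. Table 1 predicts lower cure with higher CRP, not an effect specific to the short course.
- That serum values could never be used. The documents are silent on this.

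**Conclusion.** The point holds as an inconsistency between two sections, with a consequence for the CRP analyses only. As written, children with a measured serum CRP are asked for saliva by one section and passed over by the other; under the second they have no value in any salivary-CRP analysis, including one that Table 1 labels entire-cohort.

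The size is unknown. The percentages in the table rest on an assumed share tested, an assumed shift and a normal log CRP; they show what could happen, not what has happened. A reader might infer that the trial's main result is compromised. It is not: the main primary analysis, the sample size and the balance of the arms are unaffected. This is a worthwhile, inexpensive correction and not a threat to the trial's main conclusion.

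**What to change.** In Other testing, delete the condition on serum CRP and request optional saliva from every participant, so that the section matches Screening, enrolment, and randomization.

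Recruitment has been under way since August 2016 and about 60 pilot participants are rolled over, so some children may already have serum CRP only. Report their number by arm beside each CRP analysis, and describe the CRP results as applying to children with a saliva value, not to the entire cohort.

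The cost is a sponge held in the mouth for 60–90 seconds and one assay for what is probably a minority of children. No blood is drawn and the sample stays optional. The change has to be made at collection, since analysis cannot replace a sample that was not taken.

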### Data handling

Data will be stored electronically in the secure Research Electronic Data Capture (REDCap) web-based platform on a server hosted at the Department of Pediatrics at McMaster University. Only research team members will have access to the data platform, and each team member will be granted access through a secure login by the study PI or his proxy. All entries will be double-checked, ranges will be checked for selected covariates, and quality will be assessed periodically using custom data queries. All subject-related information including case report forms, laboratory specimens, evaluation forms, reports, etc. will be kept strictly confidential. All records will be kept in a secure, locked location and only research staff will have access to the records. Subjects will be identified only by means of a coded number specific to each subject. As noted above, the REDCap study database is securely protected and encrypted. All computerized databases will identify subjects by numeric codes only. Upon request, subject records will be made available to the study sponsor, monitoring groups representative of the study sponsor, and Health Canada.

### Safety and adverse events

The investigators will report adverse events (AEs) as per standard procedure of the Hamilton Integrated Research Ethics Board (REB), the CHEO REB, and Health Canada. Specific adverse events that have a higher likelihood of being caused by amoxicillin administration include rash, diarrhoea, candidiasis, and anaphylaxis. Nausea and vomiting are commonly reported in association with amoxicillin use, though a recent meta-analysis did not find their occurrence to be any more common with amoxicillin use as compared to placebo [36]. As rash, diarrhoea, nausea, and vomiting can also be caused by inter-current infection, each participant reporting an AE will have to have their case reviewed by an investigator. Parents will be informed that any development of anaphylaxis requires immediate evaluation at the appropriate ED; should this happen while the participant is taking the second set of medication or shortly thereafter (i.e. day 6–14) the participant’s treatment assignment will be unblinded if deemed necessary per the attending physician and local PI/delegate. Anaphylaxis that occurs more than 24 h after cessation of amoxicillin (or placebo) is highly unlikely to be related to that product.

We note that adverse events associated with antimicrobials are likely to be fewer in study participants than in children whose caregivers do not agree to participate in the study; furthermore, the AEs that occur are likely to be handled more promptly. This is because the study drug we are using is the standard of care for paediatric CAP and the entire aim of the study is to verify that shorter courses of amoxicillin are non-inferior to amoxicillin given for the standard longer duration. As noted previously, we will be actively seeking drug AEs during the phone calls at day 3–5 and 7–10 and will be asking parents to fill out a daily symptom diary that will ask about potential AEs.

Specific adverse events that have a higher likelihood of being caused by short durations of antimicrobial therapy for CAP include recrudescence of CAP and symptoms associated with this, including fever, cough, difficulty breathing, tachypnoea, abdominal pain, and malaise. Having stated this, it is also not uncommon for children to experience these symptoms when contracting a new (inter-current) respiratory viral infection. We will be actively seeking evidence of potentially recrudescent infection when contacting caregivers at day 3–5 and day 7–10; additionally, we will ask caregivers to contact us if these symptoms develop. Any participant with new or worsening respiratory symptoms will have their case reviewed by the local PI and urged to see a physician, if necessary; should this physician feel that the participant might have inadequately treated bacterial CAP, and the PI concurs that unblinding will be beneficial to patient management, the participant’s treatment assignment will be unblinded.

We do not expect any AEs associated with study-related specimen collection. Nasopharyngeal swabs are routinely done at both study sites in all children admitted to hospital with a respiratory syndrome. Rectal swabs are similarly very low-risk interventions; the procedure for obtaining a rectal specimen is similar to that involved in taking rectal temperature (the reference standard for temperature measurement in young children); however, obtaining a rectal swab specimen takes much less time than rectal temperature measurement. Any AE that occurs between the times a study participant signs the informed consent form and the time the participant departs the study at the end of the final follow-up visit (or at the time of early discontinuation of the subject from the study for any reason) will be captured and recorded. AEs will be described as “pre-intervention”, “‘related”, and “serious” as applicable, but all will be recorded. Physician diagnoses of AEs as a particular syndrome (e.g. “cellulitis”) will be recorded.

All serious AEs (SAEs) that are both unexpected and related to the study product will be reported to Health Canada, and those related to the study product or procedures will be reported to the appropriate REB as soon as possible if required by the REB, but no later than 15 calendar days (7 days if fatal or life-threatening) after first knowledge of the event. Further information and significant new information on ongoing reported SAEs will be provided to the sponsor, the REB and Health Canada, as applicable. Copies of all information about the SAE will be kept in the regulatory binder.

All caregivers will be asked to complete a symptom diary form each day post-randomization until the tenth post-randomization day; questions on this form will seek information on clinical features of persistent or worsening respiratory disease (e.g. fever, difficulty breathing, overall clinical status) in addition to common (e.g. diarrhoea) and serious (e.g. anaphylaxis) AEs known to be associated with amoxicillin administration. In addition, the RA will specifically ask about symptoms and signs consistent with respiratory deterioration or amoxicillin-associated AEs. This will also be done at the time of visit 1, when the participants return to be clinically evaluated at day 14–21 post-randomization.

The SAE most likely to occur is hospitalization in the first few days post-recruitment, due to worsening respiratory status. Though the majority of children with mild CAP respond well to oral antimicrobial therapy, a small percentage will worsen and require admission to hospital because of progressive oxygenation failure and/or the need for operative drainage of pleural-based collections. These SAEs would not be related to any trial procedures, as all study participants will be receiving the first-line antimicrobial agent of choice (high-dose amoxicillin) for the first 5 days post-enrolment. We note that the risk of harm to trial participants will likely be less than to non-participants, because study staff will be contacting all study participants at intervals to verify clinical stability. As detailed above, the RAs will contact all study participants once at day 3–5 post-recruitment and once at day 7–10 post-recruitment and will be actively questioned about symptoms indicative of worsening respiratory status. Furthermore, all participants that are persistently febrile at day 4 post-recruitment will complete 10 days of open-label high-dose amoxicillin.

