### Study endpoints

#### Primary outcome

The primary outcome, early clinical cure, will be defined by meeting all of the following criteria:Significant improvement in dyspnoea and increased work of breathing, and no recorded tachypnoea, at the day 14–21 follow-up visitNo more than one fever spike (as defined above) as a result of bacterial respiratory illness from day 4 up to and including the day 14–21 follow-up visitLack of a requirement for additional antibacterials or admission to hospital because of persistent/progressive lower respiratory illness during the 2 weeks after enrolment

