For the measurement of the primary outcome, a physician or nurse, blinded to treatment allocation, will assess temperature, respiratory rate, and evident increased work of breathing, in person using standardized protocols; these physical examination findings are the most important when assessing response to therapy. Lack of fever at home will be verified through assessment of the symptom diaries. Medical visits for persistent respiratory illness will be assessed by directly asking the participant’s caregiver; though caregiver report is not an entirely reliable modality, we believe that the sensitivity and specificity of the question “Did your child see another health professional because of a concern about respiratory illness within the past ten days?” should be adequate.

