#### Follow up

The RA will phone the caregiver once at day 3–5 and once at day 7–10 to verify the clinical stability of the participant. Caregivers will also be explicitly informed that they can contact the study team in the event of a concern prior to the scheduled phone calls. The caregiver will be given a study diary to complete each day, which will include the following: temperature, dyspnoea (older participants), increased work of breathing, school attendance, caregiver absenteeism from work duties, days of mild diarrhoea, mild (abdominal discomfort, rash) and severe (anaphylaxis) drug adverse reactions, and the number of missed medication doses, if applicable. The caregivers will be instructed how to take their child’s temperature and assess increased work of breathing. Any participant who has persistent fever more than 3 days post-enrolment will receive an additional 5 days of open-label amoxicillin after the initial 5 days (i.e. will receive a guaranteed 10 days of antimicrobial agents). Any participant who worsens clinically subsequent to enrolment at any time point prior to the primary outcome visit will be urged to seek medical care without delay either at the site where recruitment took place or with another physician (e.g. family physician, walk-in clinic); all participants will be provided with printed documentation about the SAFER trial and contact information for the local Principal Investigator (PI) for the benefit of the medical professional re-evaluating the participant. The criteria for permanent discontinuation of the experimental aspect of the study protocol in an individual subject are as follows: failure to defervesce by day 4 post-enrolment; requirement for hospitalization because of worsening respiratory illness; severe reaction potentially associated with amoxicillin, such as a generalized allergic reaction (urticarial rash, bronchospasm, angioedema, hypotension, etc.); requirement for prohibited concomitant medications; completion of treatment/intervention as defined by the protocol; or clinical reasons believed by the physician to be life-threatening.

The daily symptom diary will include prompts to aid caregivers to remember the three daily doses of study medication. The RAs will also encourage optimal adherence to medication administration at baseline and at each of the two scheduled follow-up phone communications.

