The participant will return to the hospital at day 14–21 for the measurement of the primary outcome and to deliver the study diaries. At this visit, the RA will verify whether the participant developed new fever or required additional antimicrobials, and will have a physician or nurse perform a brief physical examination (temperature, respiratory rate, and assessment of increased work of breathing). The medication bottles will be returned and the volume of remaining medication determined. The RA will phone the caregiver one month after enrolment to verify continued clinical stability. All attempts will be made to follow up participants, even those who are already known to represent clinical failure (e.g. do not defervesce by day 4 post-recruitment and receive 10 days of open-label amoxicillin) or who receive additional interventions outside of the study (e.g. have additional antimicrobial agents prescribed by other clinicians) to ensure completeness of data collection (Fig. 1).

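### The diary that verifies absence of fever is stated to end on day 10, but the fever criterion runs to the day 14–21 visit, leaving 4 to 11 days to recall

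*Protocol article*

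**What the plan says.** All references are to the protocol article.

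- **Fever window** (Primary outcome): at most one fever spike attributed to bacterial respiratory illness is allowed "from day 4 up to and including the day 14–21 follow-up" visit. Table 1 likewise runs the spike count to the visit.
- **Fever source** (Primary outcome): "Lack of fever at home will be verified through assessment of the symptom diaries".
- **Diary length** (Safety and adverse events): "All caregivers will be asked to complete a symptom diary form each day post-randomization until the tenth post-randomization day". This is the only end date given. Follow up describes daily completion without an end date and has the diaries handed in at the day 14–21 visit.
- **Scheduled calls before the visit** (Follow up): "The RA will phone the caregiver once at day 3–5 and once at day 7–10 to verify the clinical stability of the participant". None is stated between day 10 and the visit.
- **Check at the visit** (Follow up): "At this visit, the RA will verify whether the participant developed new fever or required additional antimicrobials". The safety section adds that the research assistant's questions about deterioration and amoxicillin-related events are repeated then: "This will also be done at the time of visit 1, when the participants return to be clinically evaluated at day 14–21 post-randomization".
- **Antibacterials or admission** (Primary outcome): these count as failure when needed "because of persistent/progressive lower respiratory illness during the 2 weeks after enrolment". Medical visits are elicited by asking the caregiver: "Did your child see another health professional because of a concern about respiratory illness within the past ten days".

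**The concern.** The source named for verifying the fever criterion ends before the criterion does. Up to day 10 there is a prospective daily temperature record. After day 10 the same criterion depends on what a caregiver remembers at one visit, plus the temperature taken there and any unscheduled contact. The criterion is a count of spikes against temperature thresholds that depend on the route of measurement, and such a count is harder to reconstruct from memory than whether a child was ill at all.

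The timing also interacts with treatment. For children who stay on blinded study drug, active amoxicillin ends on day 5 in one arm and day 10 in the other. The first off-drug days are under the diary in the 5-day arm and outside it in the 10-day arm. If relapse tends to follow the stop of treatment, it would be recorded with different intensity in the two arms. Blinding does not remove this, because it follows from calendar time.

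The health-visit question has a separate problem: its ten-day look-back is shorter than the two-week window of the criterion it informs. Finally, Table 1 takes days of mild adverse reactions and days of absence from the diaries, so those counts also stop at day 10.

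**Working it through.** **Day counts.** I assume that days from enrolment and days from randomisation are the same count. V is the visit day.

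Fever window: V − 4 + 1 days. Diary days inside it: days 4 to 10, that is 7. Days without diary: V − 10.

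| Visit day | Window days | Diary days | Without diary | Share |
|---|---|---|---|---|
| 14 | 11 | 7 | 4 | 36% |
| 17 | 14 | 7 | 7 | 50% |
| 21 | 18 | 7 | 11 | 61% |

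**Off-drug days by arm**, blinded drug taken as assigned:

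- 5-day arm: off drug from day 6, so 9 days to a day-14 visit and 16 to a day-21 visit. Five of them (days 6–10) are under the diary.
- 10-day arm: off drug from day 11, so 4 and 11 days. None is under the diary.

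**Health-visit question.** Asked on day V, it reaches back to day V − 10: day 4 for a day-14 visit and day 11 for a day-21 visit. Of days 1 to 14 it misses days 1 to V − 11, that is 3 to 10 days. If the day 7–10 call also asks about medical visits (an assumption), a gap remains only for visits on days 19 to 21 after an early call. The extreme is a call on day 7 and a visit on day 21, which leaves days 8–10.

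**What under-recording could do.** The documents give no miss rate, so this is an illustration over an assumed range.

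The plan's own figure first. With 5% failure in both arms, margin 0.075, one-sided alpha 0.025 and 80% power:

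n = (1.960 + 0.842)² × (2 × 0.05 × 0.95) / 0.075² ≈ 133 per arm, against 135 stated. This agrees within 3% and is not disputed. Power at 135 per arm is 80.7%.

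The probability of declaring non-inferiority is Φ[(0.075 − (pT − pC))/SE − 1.960], with SE = √[pC(1−pC)/135 + pT(1−pT)/135]. Let u be the share of all failures that go unrecorded.

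Example: true rates 12.5% and 5%, u = 20% in both arms. The recorded rates are 10% and 4%, SE = 0.0308, and Φ(0.015/0.0308 − 1.960) = 7.0%.

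| u | False non-inferiority at 12.5% vs 5%, both arms under-recorded | Same, only 10-day arm under-recorded | Power at 5% vs 5%, only 10-day arm under-recorded |
|---|---|---|---|
| 0 | 2.5% | 2.5% | 80.7% |
| 10% | 4.2% | 1.8% | 77% |
| 20% | 7.0% | 1.2% | 73% |
| 30% | 11.8% | 0.8% | 69% |

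The two patterns pull in opposite directions. Equal under-recording shrinks the difference and favours non-inferiority; under-recording in the 10-day arm alone works against it.

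**The case against.** The strongest reply is that late fever is not lost. The research assistant checks for new fever and additional antimicrobials at the visit, with no look-back limit stated. The symptom questions are repeated there, a blinded physician or nurse examines the child, and caregivers are told to make contact if concerned. Data collection is identical in both arms on every calendar day. The day-10 end date appears once, in the safety section, and the full protocol and diary form are not shown.

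Much of this stands, and it rules out several stronger readings that a reader might infer:

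- **That late relapse is missed.** The text provides for retrospective capture. What is lost is the daily record.
- **That the ten-day question creates the same split at day 10.** Asked at the visit, it covers the late days and misses the early ones. It concerns seeing a health professional, which is not itself a failure criterion. The separate check on antimicrobials and the calls partly fill the gap, days 8–10 remain diary days for fever and breathing, and the antibacterial/admission criterion ends at two weeks, not day 21.
- **That late drug reactions are dropped.** Adverse events are recorded to the final follow-up visit. Only the diary-based day counts are cut off.
- **That the trial is biased against the 5-day arm.** This needs relapse to cluster after the stop of drug, and the article gives no data on relapse timing.

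The mismatch itself is not answered. No passage extends the diary beyond day 10, and the visit check is described as establishing whether fever occurred, not as counting spikes. The article itself concedes that caregiver report is not fully reliable, though it says so of medical visits and judges its question adequate.

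**Conclusion.** The concern holds as a mismatch in how the primary outcome is ascertained. As written, the source named for the fever criterion covers 7 of its 11 to 18 days, and the remaining 4 to 11 days depend on recall at the visit. The health-visit question falls 3 to 10 days short of the two-week window, with partial cover from other checks. Capture could differ by arm because the 10-day arm's off-drug days all fall after the diary ends, but the documents settle neither the direction nor the size of any bias. The error-rate figures above rest on an assumed 10–30% under-recording; they show sensitivity and estimate nothing about this trial. The sample size is unaffected. The point merits correction while recruitment is open, because days not recorded prospectively cannot be recovered later.

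**What to change.** Reconcile the Primary outcome, Follow up and Safety and adverse events sections as follows:

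1. Extend the daily diary to the day of the primary outcome visit, at least for temperature, breathing, absence from school or work, and adverse reactions. State that end date wherever the diary is described.
2. Reword the caregiver question to cover the whole period since enrolment, and ask for the date of every health visit, antibacterial prescription and admission.
3. For children already enrolled, including the roughly 60 carried over from the pilot, record which days of the fever window the diary covered. Add a sensitivity analysis of the primary outcome by diary coverage.

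The cost is 4 to 11 further diary days per caregiver, a reprinted form, one reworded question and a minor amendment. No extra visits, staff or procedures are needed.
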